Bangladesh has a patriarchal society that is dominated by men [10]. The topic of menstruation is taboo in society [11]. During follow-up, there is a substantial risk of participant loss, particularly for the male counterparts. When taken into account in the socio-cultural context, those lost to follow-up are regarded as 30%. Considering the lost-to-follow-up rate, a total of 156 (78 - intervention and 78 - control) women and adolescent girls with disabilities were recruited in the study.

Recruitment Process

Two community health workers have been recruited for the study from the 'Organization of People with Disabilities'. The lead investigator provided them with training and supportive supervision. 'Organization of People with Disabilities' is a root-level organization that especially works for people with disabilities at the community level. The recruited community health workers will meet with community members door-to-door. They will use "Washington Group Short Set Questionnaires on Functioning” for disability screening. The questionnaire set has questions on visual, hearing, walking, concentration, communication ability, and self-care [12]. It is a disability identification tool using which it is possible to identify those who are at risk of disability. From the positively screened individuals with disabilities, study participants will be recruited. Male counterparts’ involvement will be considered a critical intervention in the study. In the intervention group, male counterparts (father, husband, and brother) of the women and adolescent girls with disabilities will also be included as study participants. The study will consider these male peers' involvement and participation in managing menstrual hygiene as the key interventions. The study will run from April 2022 to March 2025.

Interventions

Figure 1 shows the procedure of the study. The intervention group will receive 10 months of health education on menstrual hygiene management as well as the role of male counterparts in managing menstrual health and hygiene. Blinding will not be used in this study. Community health workers will visit the study participants on a door-to-door basis. They will provide health education information in one-on-one meetings and courtyard sessions.

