The Multi-dimensional Scale of Perceived Social Support will be used to assess perceived social support among women and adolescents with disabilities. The multi-dimensional scale of perceived social support is divided into three sub-scales: family subscale, friends subscale, and significant other subscale. Any mean scale score between 1 and 2.9 could be regarded as low support while scores between 3 and 5 could be regarded as moderate support. and scores between 5.1 and 7 might be regarded as high support [18,19]. The Bangla version of the scale will be used.

Data collection and follow-up

We will collect data at baseline, after 10 months of health education intervention. The data collection tool will be the Kobo Toolbox, which is a real-time data collection tool [20]. The researchers are using the Kobo Toolbox as a data collection and monitoring instrument. Community health workers will go door-to-door. Participants will be interviewed one-on-one. The interview will be performed utilizing a Kobo Toolbox-embedded questionnaire.

Methods of Monitoring

Global positioning system mapping will be embedded in the questionnaire for monitoring purposes. In addition, community health workers will send activity photos and recorded interviews with the prior consent of the participants. Triangulation of the GPS map, photos, recorded audio files, and real-time communication with field staff will ensure quality data collection and following steps. Principal investigators will visit the fields periodically if needed.

Data Quality Control

Data cleansing will be done following data collection. It covers handling missing values, outliers, and inconsistencies. Accuracy, consistency, and dependability will be ensured by performing checks on data validation, reconciliation, and profiling. To increase confidence in the data and ensure trustworthy insights, a thorough data quality control method will be used.

Data Analysis Plan

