One limitation is that the study focuses only on women and girls with disabilities in selected sub-districts of Bangladesh, limiting the ability to generalize the findings to the wider population of women and adolescent girls with disabilities. Second, it uses a quasi-experimental design, which does not fully control for confounding variables that could impact the results. A randomized controlled trial would provide more robust evidence of the effects of male involvement. There may be a lack of longitudinal data to determine if the effects of male involvement are sustained over the long term. The study will measure the impact immediately after the intervention. Lastly, there is a chance of social desirability bias in the study. To reduce the limitations in the future based on available funding, more study sites will be recruited with larger sample sizes, and even researchers will think about a randomized controlled trial. To reduce social desirability bias, a congenial environment will be ensured so that female counterparts can respond freely without feeling any coercion.

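### Community health workers both teach the intervention group and collect its self-reported outcomes, unblinded; who interviews whom is not stated, and any reporting bias that differs between groups enters the treatment effect

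*Protocol article*

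**What the plan says.** The statements that bear on this point are spread over several sections of the protocol article.

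- **Recruitment Process:** "Two community health workers have been recruited for the study". They come from an organization of people with disabilities, are trained and supervised by the lead investigator, and screen for disability door-to-door. No other study field staff are named.
- **Interventions:** "The intervention group will receive 10 months of health education on menstrual hygiene management". On delivery: "Community health workers will visit the study participants on a door-to-door basis", and "They will provide health education information in one-on-one meetings and courtyard sessions". On masking: "Blinding will not be used in this study".
- **Interventions, control group:** control women receive routine family planning services from a government directorate, which has community health workers of its own.
- **Scales of measurement/screening:** the outcomes are three questionnaire scales answered by the woman herself (menstrual practice needs, perceived stress, perceived social support), each taken before and after the intervention.
- **Data collection and follow-up:** "Community health workers will go door-to-door. Participants will be interviewed one-on-one". Under Methods of Monitoring, the workers send in recorded interviews, which are compared with GPS data, photos and contact with field staff.
- **Strengths and limitations:** social desirability bias is named as a limitation, with this remedy: "To reduce social desirability bias, a congenial environment will be ensured". The effect is measured immediately after the intervention ends.

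**The concern.** Teaching and outcome measurement are both given to community health workers, and two are named. Unless there are interviewers whom the article does not mention, an intervention woman will be asked how well she manages menstruation by someone from the small team that has just spent ten months teaching her to manage it. She may wish to please her teacher, and the teacher may expect improvement. Control women are taught by the directorate, so they would not normally have this tie to the interviewer.

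A reporting bias of equal size in both groups cancels in the comparison of changes. A bias that is larger in the taught group at follow-up does not cancel. It adds directly to the group-by-time interaction, the effect on which the sample size was built. At stake is whether a positive result can be told apart from courtesy towards the educator.

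**Working it through.** **Step 1: Do the roles overlap?** Interventions gives the teaching to community health workers. Data collection and follow-up sends community health workers door-to-door and has participants interviewed one-on-one, and Methods of Monitoring has the same workers submit the recordings. Recruitment Process names two workers and no other interviewers. Overlap is therefore the plain reading, but it is an inference, because no section pairs a worker with a woman. That control women are interviewed by someone who did not teach them is a second inference, from the separate source of their education.

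**Step 2: Reproduce the planned size.** Inputs from the article: effect size f = 0.13, repeated-measures ANOVA with within-between interaction (Sample Size), 120 women, 60 per group (Abstract), two time points. Not stated and therefore assumed: two-sided alpha 0.05, power 0.80, pre-post correlation rho = 0.5.

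- Noncentrality: lambda = f² × N × m / (1 − rho), with m = 2 and degrees of freedom 1 and N − 2.
- At N = 120: lambda = 0.0169 × 120 × 2 / 0.5 = 8.11, which gives power 80.6%.
- The smallest even N that reaches 80% is 120, so the article's figure is reproduced. At rho = 0.3 the same target needs 166, and at rho = 0.7 it needs 72.

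With two groups and two times, f equals the between-group difference in mean change, in SDs of the score, divided by 4. The planned effect is therefore 4 × 0.13 = 0.52 SD.

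**Step 3: Enter a purely differential reporting shift.** Set the true effect to zero and let the intervention group's follow-up scores move by b SD through reporting alone. Then f = b/4 and lambda = (b/4)² × 120 × 2 / (1 − rho) = 15b² / (1 − rho).

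| Assumed shift b | Share of 0.52 SD | Significant, rho 0.3 | rho 0.5 | rho 0.7 |
|---|---|---|---|---|
| 0 | 0% | 5.0% | 5.0% | 5.0% |
| 0.1 SD | 19% | 7.4% | 8.4% | 10.8% |
| 0.2 SD | 38% | 15.1% | 19.2% | 28.9% |
| 0.3 SD | 58% | 28.1% | 37.1% | 55.7% |

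The documents give no size for the shift. The table shows sensitivity and is not an estimate.

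**Step 4: Do the planned measures remove it?**

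- *Confounder adjustment* (Data Analysis Plan) acts on participant characteristics. This bias is an error in measuring the outcome that arises after the teaching starts, so neither covariates nor the baseline score carry it.
- *A congenial environment* is meant to let women answer freely and without coercion. It does not change who is asking.
- *Audio recordings and supervision* can reveal leading questions or miscoding. They cannot reveal an answer shaded to please.

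**The case against.** The strongest case on the other side has four parts.

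1. *The article never says that a woman's own teacher interviews her.* This stands as a limit. The interview sentence is in the passive, the procedure figure is not shown, and field assignment could sit in a fuller document. But the article itself gives both tasks to one cadre and names two workers, so the ambiguity is in its own text. A reader might go further and take it as established that every control woman is interviewed by a stranger to her. The documents do not say so. They also call the directorate's field staff community health workers.

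2. *Safeguards exist beyond the congenial environment.* This is correct. Training, supervision, recorded interviews and their triangulation are partial protection against interviewer leading, so it would be wrong to call the congenial setting the only safeguard. They do not deal with a respondent's wish to please.

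3. *Social desirability is not confined to follow-up or to the intervention group.* This is also correct. The topic is taboo, everyone is briefed on the objectives before consent, and the study workers meet participants at screening. Bias can be present at baseline and in controls. A reader might infer that it acts only at follow-up and only in the taught group, and the documents do not support that. The point rests on the differential part alone.

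4. *The authors disclose the weaknesses.* They state that there is no blinding, name social desirability bias and say that a randomized trial would be more robust. The disclosure is general. It does not address the possibility that the bias differs between groups because educator and interviewer coincide.

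**Conclusion.** The point holds as a weakness that should be corrected. The article assigns ten months of education and the unblinded outcome interviews to the same cadre, names two workers, and does not say who interviews whom. Followed as written, this risks a differential reporting bias in the group-by-time effect that the planned analysis and monitoring cannot remove.

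Its size is unknown. If the differential shift were 0.1 to 0.3 SD, about a fifth to three-fifths of the planned 0.52 SD, the chance of a significant result with no true effect would rise from 5% to between 8% and 37% at a correlation of 0.5, and to between 7% and 56% over correlations of 0.3 to 0.7. These figures assume 60 analysed per group, alpha 0.05, and a shift in the intervention group alone. A reader might take 8%, 19% and 37% as the trial's actual false-positive rates. The documents do not support that, since they state neither the shift nor the correlation.

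**What to change.** In Data collection and follow-up, state that no woman is interviewed by the worker who delivers her sessions, and arrange the field work as follows.

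- Give each of the two workers a separate set of intervention women to teach, including for courtyard sessions, and have the other worker do those women's outcome interviews.
- Where baseline is not yet done, use the same interviewer at baseline and at 10 months. Changing interviewer at follow-up mainly in the intervention group would create a new interviewer-by-time difference between the groups. Where baseline is already done, record who did it and take any change of interviewer into account.
- Split the control interviews between both workers in the same way, so that interviewer is not tied to group.
- Record interviewer identity at each visit and examine interviewer effects in the analysis.
- Do not bring in self-entry on the device at follow-up only, or only for the women able to use it. That would mix response mode with time, or with the disability types that the analysis compares.

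No new staff are needed. The cost is extra travel and coordination between sites. The gain is partial, because the interviewer still belongs to the study team and may learn the group. If both workers must teach the same women, the article should say so and name the remaining bias as a limit on the conclusion. If separate interviewers already exist, one sentence saying so, and that they serve both groups, would largely settle the point.

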## Results

The result of the study will be published in a scientific journal. The outcomes of the research will be disseminated to local policymakers and health planners. The health administrator will get evidence-based information on gender-inclusive menstrual hygiene management for women and adolescent girls with disabilities through research result dissemination events.

## Discussion

Women and adolescents with disabilities face many types of challenges. Challenges during their menstruation days are some of the worst challenges they have to face [23]. They have to rely on family members to different extents based on their disability types and severity [24]. They face difficulty in getting menstrual products and treatment during menstruation if male peers are unaware of menstrual needs [25,26].

In many low- and middle-income countries (LMICs), men are the primary decision-makers [27]. It is important to engage male counterparts in the sexual and reproductive healthcare issues of female peers. It is evidenced in different studies that their involvement created positive outcomes. In developing nations, male involvement can lead to better maternal health outcomes, according to a systematic review and meta-analysis by Yargawa et al. [28]. A study conducted by Atwine et al. in 2017 found that male involvement was associated with the normal nutritional status of under-five children in Uganda [29]. Another study conducted by Yemata et al. in 2023 found that husband participation in birth preparedness and complication readiness was beneficial for pregnant mothers [30].

There are significant practical ramifications to the quasi-experimental study investigating the participation of male counterparts in the management of menstruation hygiene for women and adolescent girls with disabilities. These results can guide the creation of programs and regulations meant to promote an environment that is more welcoming and encouraging, especially for women and adolescent girls with disabilities. The study's inclusion of male partners may aid in eradicating stigmas associated with menstruation and advancing gender equality. Culturally, males are not only breadwinners but also act as protective shields for their female counterparts in Bangladesh. When men are well informed and take part in MHM, their involvement will provide a protective shield against negative attitudes toward their female counterparts. In turn, these can enhance the general well-being of women and girls with disabilities by giving them access to the tools and emotional support they need during their menstrual cycles. In conclusion, this study emphasizes the importance of identifying and meeting the particular needs of this group of people, which will ultimately lead to improved menstrual hygiene management and increased gender justice.

Strengths and limitations

The study offers a number of significant benefits. First, by highlighting the participation of male counterparts in menstrual hygiene management (MHM) of women and adolescent girls with disabilities, it fills a critical study gap. Inclusive MHM can ensure quality MHM for women and adolescent girls with disabilities. As a result, their quality of life will be improved. The negative health outcomes due to non-hygienic MHM will be reduced. Thus, in turn, their family and society will also benefit. In other words, the overall burden due to non-hygienic MHM will be reduced, especially in the case of women and adolescent girls with disabilities in selected sub-districts of Bangladesh. These viewpoints are especially essential since they emphasize how crucial it is to include men in MHM practices, dismantling conventional taboos, and creating a welcoming environment. Additionally, the study adopts a quasi-experimental design, allowing for a comparative analysis of outcomes between the intervention and control groups. Three scientifically proven scales of measurement are being used. These methodological approaches will increase the study's validity and contribute to the evidence base by quantifying the influence of male engagement in MHM.

Furthermore, the study takes place in selected sub-districts of Bangladesh, an area with less research on this topic, making it an important contribution to the region's understanding of menstruation health and disability. The protocol will ensure ethical considerations are followed properly, promoting the dignity of the study participants. Overall, these strengths will make this study a significant step toward advancing the field of gender-inclusive MHM.

One limitation is that the study focuses only on women and girls with disabilities in selected sub-districts of Bangladesh, limiting the ability to generalize the findings to the wider population of women and adolescent girls with disabilities. Second, it uses a quasi-experimental design, which does not fully control for confounding variables that could impact the results. A randomized controlled trial would provide more robust evidence of the effects of male involvement. There may be a lack of longitudinal data to determine if the effects of male involvement are sustained over the long term. The study will measure the impact immediately after the intervention. Lastly, there is a chance of social desirability bias in the study. To reduce the limitations in the future based on available funding, more study sites will be recruited with larger sample sizes, and even researchers will think about a randomized controlled trial. To reduce social desirability bias, a congenial environment will be ensured so that female counterparts can respond freely without feeling any coercion.

## Conclusions

The study may have a lot of potential. This study may provide important insights into enhancing the general well-being and dignity of this vulnerable population by examining the impact of male involvement in menstrual hygiene management, particularly among women and adolescent girls with disabilities. The result of this study may influence policies and programs that work to break down menstrual taboos and advance a more inclusive, egalitarian, and healthy society in Bangladesh and worldwide.
